## METHODS

### Design and ethics

PRoVENT-PED is an investigator-initiated, long-term, prospective, international, multicenter study that will collect detailed respiratory support data biannually over 10 years during predefined 4-week intervals, with an optional additional period to accommodate data collection during epidemics or pandemics. International and regional networks of pediatric intensivists and respiratory therapists are responsible for recruiting participating centers. Study coordinators guide national and regional coordinators in acquiring ethical approval, and help in the administrative processes. Due to its observational nature, participation may not require individual patient consent in most nations or regions; however, this depends on national and regional legislation, and local policies of the participating centers. The study protocol was initially approved by the Institutional Review Board of the University Medical Center Groningen, the Netherlands (METc 2023/375). PRoVENT-PED is registered at Clinicaltrials.gov (study identifier NCT06220825). PRoVENT-PED complies with the International Conference on Harmonization-Good Clinical Practice (ICH-GCP).

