### Randomization

To prevent larger centers from disproportionately influencing the findings, we will implement randomization in centers expected to enroll more than one hundred patients during a given period, based on the focus of each phase.

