### Statistical analysis

Descriptive statistics will be used to describe patient demographics and baseline characteristics, types of respiratory support used, device settings, and respiratory variables and parameters, including measures of oxygenation and decarboxylation. Continuous variables will be expressed in medians and interquartile ranges, and categorical variables will be expressed in frequencies and proportions. The Kruskal-Wallis test will be used to compare continuous variables, and the Chi-squared test will be used for categorical variables.

Respiratory support settings and respiratory variables and parameters at successive days will be reported in detail for the first days of respiratory care and compared between different age groups, i.e., neonates (< 1 month), infants (1 month to < 12 months), toddlers (12 months to < 3 years), preschoolers (3 years to < 6 years), school-age children (6 years to < 12 years), and adolescents (12 years to 18 years). Additionally, respiratory support settings, respiratory variables, and ventilation parameters will be compared between patients with and without PARDS and across other patient groups, including patients receiving respiratory support due to a pulmonary disease *versus* non-pulmonary conditions and patients receiving ECMO.

Key respiratory support settings, respiratory variables, and parameters will be visualized using cumulative distribution plots for the first days and line graphs over successive days. Inpatient trends over time are assessed with mixed-effect linear models with patients treated as a random effect to account for clustering and repeated measurements, and with day, different patient group and their interaction as fixed effects. P values from this analysis represent the overall difference among different patient groups over time, and p values from interaction represent the difference in trend over time among the different patient groups.

Time-to-event outcomes, like liberation from the ventilator, discharge and death, will be presented in Kaplan-Meier curves. Cox proportional hazard modelling or competing risk analyses will be used to study associations with continuous clinical outcomes, presented as hazard ratios (HR) and 95% confidence intervals (95%CIs). Logistic regression will be used to study the association between key ventilator settings and ventilation parameters and binary clinical outcomes, and will be presented as odds ratios (OR) and 95%CIs.

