A robust locally weighted scatter plot smoothing (LOWESS) method will be used to investigate the association between ICU mortality and key ventilatory variables and parameters, including V^T^, Ppeak, PEEP, FiO^2^, RR, PaO^2^/FiO^2^, ΔP, MP and ME. The smoothing curves will be generated with a bandwidth of 0.66, a polynomial regression with 1 degree of freedom, and a tricubic weighting function so that observations furthest from the point of interest are assigned the least weight.

In a univariate analysis, the impact of the single key ventilatory variables on mortality will be assessed by estimating the relative risk of all-cause 28-day ICU mortality. Multivariate logistic regression will be used for the adjusted analysis, adjusting for unequal distribution of effect modifiers. We will adjust for baseline covariates selected according to clinical relevance, including age, sex, weight, comorbidities, and severity of illness. Results will be shown as ORs with 95%CI. Multiple imputation will be performed to account for missing values.

Data will be analyzed with R version 4.2.2 (R Core Team, 2022, Vienna, Austria). Statistical uncertainty will be expressed by 95%CIs. A p value < 0.05 is considered statistically significant.

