The proposed study offers several strengths. PRoVENT-PED's adaptive design allows for a flexible focus on evolving clinical priorities, enabling the investigation of key topics such as invasive and noninvasive ventilation, weaning, patient-ventilator asynchronies, and extracorporeal support. Once the required sample size for one topic is reached, the study can seamlessly transition to the next, ensuring responsiveness to emerging challenges in pediatric intensive care. Its prospective design ensures more accurate data collection on exposures, confounders, and outcomes compared to retrospective studies, reducing the risk of bias and improving the reliability of the findings. The planned large sample size is expected to provide robust insights into associations between ventilation practice and clinical outcomes. By including diverse ICUs across resource-limited and resource-rich settings worldwide, the study captures variations in practice, patient populations and ventilation strategies, enabling exploration of geo-economic differences and their impact on outcome. Additionally, data collection across different seasons and patient groups will allow for comprehensive subgroup analyses, including patients with and without PARDS, various age categories, and diverse disease conditions.

A pilot study was conducted to test the feasibility of data collection and assess the presence of missing data. Most data were effectively captured. Notably, the absence of specific data does not necessarily indicate missingness but may reflect clinical practice. For instance, blood gas analyses might not have been performed if not clinically indicated, and such cases were not classified as missing data. In contrast, variables like patient height, which should have been recorded but were not, were treated as genuinely missing. This distinction was carefully accounted for in the analysis. Furthermore, the time required for data collection was considered sufficiently low, even when accounting for settings such as low- and middle-income countries (LMICs), where the time available for such tasks may be more limited.

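### The only stated allowance for clustering is a patient random effect; no stated model accounts for correlation between children treated in the same ICU.

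*Protocol article*

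**What the plan says.** Under Design and ethics the article describes its structure: "PRoVENT-PED is an investigator-initiated, long-term, prospective, international, multicenter study". Children are therefore nested in ICUs, and ICUs in countries.

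The Statistical analysis section then describes three kinds of model:

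- **Daily trends.** These use "mixed-effect linear models with patients treated as a random effect to account for clustering and repeated measurements", "with day, different patient group and their interaction as fixed effects". No ICU, country or region term is named.
- **Time to event.** "Cox proportional hazard modelling or competing risk analyses will be used to study associations with continuous clinical outcomes". No frailty, stratification or robust variance by ICU is named.
- **Binary outcomes, including mortality.** "Logistic regression will be used to study the association between key ventilator settings and ventilation parameters and binary clinical outcomes". For the adjusted mortality model: "We will adjust for baseline covariates selected according to clinical relevance, including age, sex, weight, comorbidities, and severity of illness". ICU, country and region are not on that list.

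One other section deals with centres. Under Randomization, "we will implement randomization in centers expected to enroll more than one hundred patients during a given period", so that large centres do not dominate the findings.

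The Discussion reports that adult studies found marked practice differences between geo-economic regions, expects similar variability in children, and names as a strength of the study "enabling exploration of geo-economic differences and their impact on outcome".

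**The concern.** The article says its patient effect deals with clustering. In a study with repeated days per child and many children per ICU there are two levels of clustering, and a patient effect handles only the lower one. Two children ventilated in the same unit share protocols, staff and resources. Nothing in the stated models lets their data be correlated.

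Two consequences follow for the main aim of the initial phase, which is to find modifiable factors independently associated with ICU mortality:

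1. **Precision.** If an exposure and the outcome both vary between ICUs, a model that assumes independence understates the standard error. Intervals are too narrow, and more than 5% of null factors reach significance.
2. **Confounding.** If ICUs with a given ventilation style also differ in mortality for reasons that the listed covariates miss, that difference enters the odds ratio for the setting.

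The Randomization section answers neither. It limits how many patients a large centre contributes; it does not model correlation among those who remain.

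**Working it through.** **The plan's own figure.** Ten factors × 10 events = 100 deaths. At 3% ICU mortality, 100 / 0.03 = 3,334 patients after rounding up, against 3,000 stated; 3,000 × 0.03 = 90 deaths. That gap is a separate matter. What counts here is that the calculation contains no design effect.

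**Inputs from the article.** N = 3,000, mortality 3%, significance at p < 0.05.

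**Inputs assumed, because the article gives none.**
- 100 ICUs × 30 patients, or 30 ICUs × 100 patients.
- Between-ICU SD of the log-odds of death: 0.5 or 0.8.
- Exposure ICC (share of exposure variance lying between ICUs): 0.1, 0.3 or 1.0. The last is a factor that is constant within an ICU.

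**Check 1: simulation under a true null.** Ordinary logistic regression, 600 runs per setting, ICU mortality effect independent of exposure. Cells give true SE / model SE, then the real error of a nominal 5% test.

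| Exposure ICC | 100 × 30, SD 0.5 | 100 × 30, SD 0.8 | 30 × 100, SD 0.5 | 30 × 100, SD 0.8 |
|---|---|---|---|---|
| 0.1 | 1.00; 4.5% | 1.07; 7.3% | 0.99; 4.7% | 1.06; 6.8% |
| 0.3 | 1.06; 6.2% | 1.13; 8.7% | 1.12; 6.0% | 1.26; 12.2% |
| 1.0 | 1.10; 7.0% | 1.30; 13.7% | 1.40; 15.0% | 1.90; 26.7% |

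The Monte Carlo standard error near 5% is √(0.05 × 0.95 / 600) = 0.9 percentage points, so the row for exposure ICC 0.1 is close to nominal.

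**Check 2: formula.** With m patients per ICU, the design effect is DE = 1 + (m − 1) × ICC_outcome × ICC_exposure, and the real error is 2(1 − Φ(1.96/√DE)). The outcome ICC must be on the 0/1 scale. To first order it is SD² × p(1 − p), with p(1 − p) = 0.03 × 0.97 = 0.0291:
- SD 0.5: 0.25 × 0.0291 = 0.0073.
- SD 0.8: 0.64 × 0.0291 = 0.0186.

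At exposure ICC 0.3:
- m = 30, SD 0.5: DE = 1 + 29 × 0.0073 × 0.3 = 1.06, error 5.7% (simulated 6.2%).
- m = 100, SD 0.8: DE = 1 + 99 × 0.0186 × 0.3 = 1.55, √DE = 1.25, error 11.6% (simulated 12.2%).

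At exposure ICC 1.0, m = 100, SD 0.8: DE = 1 + 99 × 0.0186 = 2.84, error 24.5% (simulated 26.7%). The two checks agree.

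**Check 3: confounding.** Same simulation, still no true effect, but with the ICU's exposure level correlated 0.3 (assumed) with its mortality effect, and no covariates:

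| Exposure ICC | Spurious OR per SD | Real error |
|---|---|---|
| 0.1 | 1.05-1.08 | 7.3-11.5% |
| 0.3 | 1.08-1.14 | 13.3-26.2% |
| 1.0 | 1.16-1.26 | 27.5-55.5% |

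The listed covariates would absorb some of this in practice.

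**The case against.** **The article is condensed and the full analysis plan is not shown.** The logistic and hazard models get one sentence each, the covariate list is open-ended, and variance estimation is often left to the plan. This has weight: silence about the logistic and Cox models does not prove that ICU will be ignored. But the article is not silent about clustering as a whole. It names the device meant to handle it, and that device is the patient. Run as written, the plan treats children in the same ICU as independent.

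**The size may be small.** This also stands in part. At exposure ICC 0.1 the effect on error is negligible. A reader might infer far larger inflation by assuming an outcome ICC of 0.10. At 3% mortality that means a between-ICU SD of √(0.10 × 0.0291) = 5.4 percentage points around a mean of 3%, which is hard to credit. The figures above use smaller heterogeneity for that reason.

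**The worst case concerns an analysis that is not specified.** Correct. The geo-economic comparison appears as a possibility in the Discussion and not in the Statistical analysis section. Nor does the article say that it expects mortality to differ between ICUs; its stated expectation concerns practice. The ICU-level row of each table is therefore conditional on such an analysis being done.

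**Case mix is adjusted for.** Partly. Age, sex, weight, comorbidities and severity cover patient-level differences. What remains is residual difference between units, so the right statement is that ICU can confound, not that it does.

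**Large centres are handled.** Only their weight is. A reader might go on to infer from the pilot's enrolment that the threshold of one hundred patients would rarely apply. Two Dutch ICUs, without stated enrolment days, cannot show that, and the rule varies with the focus of each phase. That rule is not part of this point.

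**Conclusion.** The point holds in conditional form. The stated clustering structure stops at the patient, no stated model has an ICU term, and the centre randomization does not supply one. Understated standard errors are the expected direction for exposures that cluster by ICU, and residual confounding by ICU is possible.

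Under the assumptions above, the real error of a nominal 5% test rises little at exposure ICC 0.1 (4.5-7%), moderately at 0.3 (6-12%), and clearly for a factor constant within an ICU (7-27%). Every ICC, ICU count and cluster size behind these ranges is assumed. They apply to the logistic mortality model; no figure was derived for the daily linear models, whose contrasts are between patient groups, or for the hazard models. A change should be made, but the documents do not support saying that the results will be invalid.

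**What to change.** - **Daily mixed models:** random effects for ICU and for patient nested within ICU.
- **Logistic mortality models:** one ICU random intercept, or generalised estimating equations with ICU-clustered robust errors.
- **Cox or competing-risk models:** shared ICU frailty, or variance clustered by ICU.
- **Where confounding by ICU is the concern:** enter each exposure as the ICU mean plus the patient's deviation from it, and base the modifiable-factor conclusion on the within-ICU term. Robust errors alone change only the standard error, and a random intercept does not in general remove between-ICU confounding.

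The cost is analysis wording and code. No new data are needed, since the pilot already reports patients by centre. Intervals will be wider where clustering matters. The structure should stay simple: at 30 patients per ICU and 3% mortality there are 30 × 0.03 = 0.9 deaths per ICU, so about 100 deaths will not support elaborate nesting. Plan for one ICU intercept, and state in advance that clustered robust errors will be used if that model does not converge.

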The most used ventilation mode was PCV (92%) (Table 2). Most patients received V_T_ of less than 8mL/kg, with younger children receiving lower median V_T_ than older patients (Figure 2). Younger patients received lower median PEEP than older patients. Median FiO_2_ and median RR were higher, and median ΔP was lower in younger children. PARDS patients received lower V_T_, higher median PEEP and FiO_2_, and lower median ΔP than non-PARDS patients.

**Table 2 t2:** Ventilator settings, ventilation variables and parameters, and arterial blood gas analysis at day 0

		All n = 125	Neonates n = 10	Infants n = 61	Toddlers n = 14	Preschoolers n = 8	School-aged n = 16	Adolescents n = 16
Ventilation mode								
	Volume controlled ventilation	9 (7)	0 (0)	0 (0)	0 (0)	1 (13)	5 (31)	3 (19)
	Pressure controlled ventilation	115 (92)	10 (100)	60 (98)	14 (100)	7 (88)	11 (68)	13 (81)
	Volume support	1 (1)	0 (0)	1 (2)	0 (0)	0 (0)	0 (0)	0 (0)
Ventilator settings								
	V_T_ (mL/kg ABW)	6 [5 - 7]	6 [5 - 6]	6 [5 - 7]	7 [4 - 8]	9 [7 - 9]	7 [6 - 8]	6 [5 - 7]
	PEEP (cmH_2_O)	6 [5 - 8]	7 [5 - 8]	6 [5 - 8]	7 [6 - 8]	7 [6 - 8]	6 [5 - 8]	7 [5 - 9]
	RR (breath/min)	30 [25 - 36]	36 [35 - 38]	35 [30 - 40]	29 [26 - 33]	26 [22 - 30]	20 [20 - 25]	19 [15 - 24]
	FiO_2_ (%)	40 [30 - 50]	45 [36 - 58]	40 [30 - 50]	40 [40 - 45]	38 [29 - 45]	30 [30 - 40]	45 [39 - 63]
Ventilation variables and parameters								
	Ppeak (cmH_2_O)	23 [20 - 27]	23 [20 - 26]	24 [21 - 27]	26 [22 - 30]	24 [18 - 26]	20 [17 - 26]	21 [19 - 28]
	Pmean (cmH_2_O)	12 [10 - 14]	10 [10 - 13]	12 [11 - 14]	13 [11 - 16]	13 [10 - 15]	10 [9 - 13]	11 [8 - 13]
	etCO_2_ (kPa)	6 [5 - 7]	5 [3 - 6]	6 [6 - 7]	6 [5 - 7]	5 [5 - 5]	5 [4 - 6]	5 [5 - 6]
	C_RS_	3 [2 - 7]	1 [1 - 2]	2 [1 - 3]	4 [3 - 5]	6 [5 - 10]	15 [11 - 18]	23 [20 - 26]
	ΔP (cmH_2_O)	16 [14 - 19]	17 [12 - 18]	17 [15 - 19]	18 [15 - 22]	17 [13 - 21]	13 [10 - 18]	14 [10 - 19]
	MP (J/minute)	2 [1 - 5]	1 [1 - 1]	2 [1 - 2]	3 [3 - 5]	5 [3 - 5]	5 [4 - 8]	8 [6 - 10]
	ME (mJ/kg)	9 [7 - 11]	10 [6 - 10]	8 [7 - 10]	11 [7 - 14]	11 [10 - 14]	10 [8 - 12]	9 [7 - 10]
Arterial/capillary blood gas analysis								
	pHa	7.4 [7.3 - 7.4]	7.4 [7.3 - 7.4]	7.3 [7.3 - 7.4]	7.3 [7.3 - 7.4]	7.4 [7.3 - 7.4]	7.4 [7.3 - 7.4]	7.4 [7.4 - 7.4]
	PaO_2_ (kPa)	6.7 [6.3 - 6.7]	5.2 [5.2 - 5.3]	6.7 [6.0 - 6.7]	6.7 [6.7 - 6.7]	6.7 [6.7 - 6.7]	6.7 [6.7 - 6.8]	6.7 [6.7 - 6.7]
	PaCO_2_ (kPa)	5.8 [5.2 - 6.6]	5.8 [5.4 - 6.3]	6.6 [5.6 - 6.7]	6.1 [5.8 - 6.3]	4.5 [4.2 - 5.2]	5.1 [4.7 - 5.7]	5.2 [5.0 - 5.7]

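### The trend model for settings over time has no age term, so PARDS, pulmonary and ECMO contrasts in RR, C_RS and MP can reflect age mix

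*Protocol article*

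**What the plan says.** The Statistical analysis section of the protocol article compares respiratory settings and parameters across several groupings. One is age: the variables are "compared between different age groups", in six bands from neonates to adolescents. Separately, "ventilation parameters will be compared between patients with and without PARDS and across other patient groups"; those other groups include pulmonary against non-pulmonary reasons for support, and ECMO. Age is not crossed with any of them.

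For changes over days the plan is a linear mixed model in which the patient is the only random effect named. Its remaining terms are given in one phrase: "with day, different patient group and their interaction as fixed effects". The section also says how to read the result: "P values from this analysis represent the overall difference among different patient groups over time", while the interaction p value stands for a difference in trend.

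Adjustment for age, sex, weight, comorbidities and severity appears later in the same section, for the logistic regression on mortality only. Under Calculations, V_T and ME are expressed per kg; RR, C_RS and MP are not scaled to body size.

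**The concern.** How ventilation differs between kinds of patient is a main product of the initial phase, and the plan attaches p values to those differences at a 0.05 threshold. Some of the variables change several-fold between infancy and adolescence. If one group holds more infants than another, a model with only group, day and their interaction assigns the age difference to the group. A reader could then take an RR, C_RS or MP contrast by PARDS status as a difference in how those children are ventilated, when part or all of it comes from how old they are.

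**Working it through.** The plan states no figure to reproduce here. The check asks how large a group contrast age mix alone could produce.

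**Inputs from the documents**
- Pilot age mix (Table 2): 10, 61, 14, 8, 16 and 16 of 125 from neonates to adolescents. The share under 12 months is 71/125 = 56.8%.
- Day-0 medians in the same order: RR 36, 35, 29, 26, 20, 19; C_RS 1, 2, 4, 6, 15, 23; MP 1, 2, 3, 5, 5, 8; ΔP 17, 17, 18, 17, 13, 14.
- PARDS share 11% (Results) and planned size 3,000 (Sample size calculation): 330 versus 2,670.

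**Assumptions**
- Practice within each age band is identical in both groups, so the true group effect is zero.
- One group has the pilot age mix. The other has a share under 12 months that differs by 10 points.
- Two versions of the shift: the infants are exchanged for all older bands in pilot proportions (milder), or for school-aged children and adolescents only (steeper).
- Medians stand in for means. The within-band SD is IQR/1.349.

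**Formulas**
- Difference = 0.10 × (pilot-weighted mean under 12 months − pilot-weighted mean of the replacing bands).
- SD² = weighted within-band variance + between-band variance.
- SE = SD × √(1/330 + 1/2,670) = SD × 0.0583.
- Chance of p<0.05 = Φ(|z| − 1.96) + Φ(−|z| − 1.96), with z = difference/SE.

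**RR worked through**
- Mean under 12 months: (10×36 + 61×35)/71 = 35.14.
- Mean of all older bands: (14×29 + 8×26 + 16×20 + 16×19)/54 = 22.93.
- Mean of the two oldest bands: (20 + 19)/2 = 19.50.
- SD = √(39.9 within + 44.5 between) = 9.19, so SE = 0.536.
- Milder shift: 0.10 × 12.21 = 1.22 breaths/min, z = 2.28, chance 62%.
- Steeper shift: 0.10 × 15.64 = 1.56 breaths/min, z = 2.92, chance 83%.

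**Results for a 10-point shift**

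| Variable | <12 months | All older | Two oldest | SE | Difference, milder / steeper | Chance of p<0.05 |
|---|---|---|---|---|---|---|
| RR | 35.14 | 22.93 | 19.50 | 0.536 | 1.22 / 1.56 | 62% / 83% |
| C_RS | 1.86 | 13.19 | 19.00 | 0.471 | 1.13 / 1.71 | 67% / 95% |
| MP | 1.86 | 5.37 | 6.50 | 0.160 | 0.35 / 0.46 | 59% / 83% |
| ΔP | 17.00 | 15.19 | 13.50 | 0.286 | 0.18 / 0.35 | 10% / 23% |

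Differences are absolute. A group with fewer infants has lower RR and ΔP and higher C_RS and MP.

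The same steps for V_T, ME, PEEP, FiO2 and Ppeak give about 6 to 18%. With no age imbalance every difference is zero and the rate is the nominal 5%. At 5 points the chance for RR, C_RS and MP is about 20 to 45%; at 20 points it is close to 100%.

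With a separate variance in each group and a milder shift towards more infants, the 10-point figures are 64% (RR), 74% (C_RS) and 66% (MP), so the choice of variance matters little.

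**Limits.** This is a one-day comparison built on rounded medians from small bands (8 to 61 children). It ignores repeated measures and centre effects.

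**The case against.** The strongest reply is that this is description. A practice survey may properly report what children with PARDS actually received, whatever their age, and the protocol does not claim its group p values are independent of age. Age bands are compared separately, and age is adjusted for in the mortality regression. A condensed article may also leave covariates to a fuller plan. Most of this stands, so the crude contrast should stay. It does not remove the point, because the article names the model's terms and reads the p values as group differences, and it lists covariates where it intends adjustment.

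Two stronger readings are tempting and not supported:

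- A reader might infer that age differences will be reported as practice differences. That needs an age imbalance, and the text and tables at hand give no age distribution by PARDS, pulmonary or ECMO status.
- A reader might infer that the pilot's finding of "lower median ΔP than non-PARDS patients" arose because PARDS children were older. No ages by PARDS status are shown, and ΔP depends only modestly on age. The article also disagrees with itself on direction: the Results text says ΔP was lower in younger children, while Table 2 shows 17 to 18 up to preschool age and 13 to 14 after it.

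Nor is an effect on the interaction p value shown. Age mix biases the trend contrast only if age also changes the slope over days, and Table 2 covers day 0 only.

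**Conclusion.** The point holds in a limited form. As written, the trend model cannot separate age from group for RR, C_RS and MP, the three variables with steep age gradients in the pilot. Under an assumed 10-point imbalance in infants and no true group effect, the false-positive rate on a single day would be roughly 60 to 85% for RR and MP and 65 to 95% for C_RS, against a nominal 5%. The range depends on which older bands replace the infants.

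For ΔP (10 to 23%) and for V_T, ME, PEEP, FiO2 and Ppeak (6 to 18%) the effect is small at that imbalance, and for all variables it vanishes if the groups have the same age mix. The size rests on the assumed imbalance, on pilot medians used as means and on the 330 versus 2,670 split. That split represents PARDS only; the sizes of the pulmonary and ECMO groups are not used. The mortality analysis is not touched.

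**What to change.** - In every trend model whose group factor is not age, add the six-level age group as a fixed effect. Add age-by-day where group sizes allow; for a sparse group such as ECMO, use the age main effect alone.
- Report the age-adjusted group difference and trend beside the crude ones, and label the crude contrast as a description of what each group received.
- Show the age distribution of each comparison group, so that readers can see how much imbalance there is.
- Reconcile the Results text on ΔP by age with Table 2.

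Cost: age is already collected at admission, so no new data are needed. The models gain a few terms. The adjusted contrast answers a slightly different question from the crude one, which is why both should be reported.
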